### Data collection

Data collection will be using both the standard antenatal cards as used by the Ministry of Health and specific forms designed for the trial (copies enclosed). The antenatal cards are patient-carried cards. All laboratory results will be entered on antenatal cards as well as trial forms.

### Data management and analysis

An independent data safety and monitoring committee (DSMC) will be established to monitor this trial if the trial is approved. Data will be double-entered and verified in Microsoft Access. An interim analysis is planned for which the statistician on the DSMC will be provided with the database. Primary outcome measure is incidence of premature labour (using gestational age as determined by Ultrasound scan at booking and date of delivery). Analysis of the primary outcome will be using a two by two table and Pearson X2 statistic. Secondary outcomes include mean gestational age, perinatal mortality and birthweight. Association with anaemia status, iron status and malaria parisitaemia will be examined using logistic regression.

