The consequences of a high incidence of preterm delivery are considerable because of the contribution to neonatal mortality – 30% in one rural area of the Gambia 5 and 65% in the Mangochi study in Malawi4. In a series from Tanzania, 52% of all babies with respiratorydistress syndrome (closely associated with prematurity) died6. Prematurity also makes an important contribution to later, infant mortality, at least as significant a contribution as maternal HIV infection in one recent report from Malawi7. Where the facilities exist in hospitals for neonatal care, prematurity represents the major indication for special care, with significant health cost consequences. 8,9

Prematurity is also well recognised as conferring long-term neuro- developmental disadvantages that include, at one end of the spectrum, cerebral palsy, and at the other more subtle educational and social difficulties. It is clearly undesirable for populations already disadvantaged by poverty and high burdens of disease, to also cope with the short and long term consequences of preterm birth.

There may be an additional dimension to the problem that has not, to our knowledge been highlighted before. Women who have had one premature delivery are at increased risk of this complication recurring in future pregnancies. It is now well recognised from epidemiological work that the dangers associated with high parity are in part explained by the efforts of women at reproductive disadvantage to achieve their desired family size. It is important to investigate this possibility in Namitambo because of the much higher risk of maternal death and morbidity per pregnancy in rural Malawi – we would like to explore this further and will obtain both women’s and men’s views on these issues.

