# Methods

We propose a randomised placebo-controlled trial to assess the significance of infection as a cause of prematurity, and to test a possibly effective intervention strategy in this high-risk population. Women will be eligible for entry into the study if they have a single viable pregnancy with fetal measurement (biparietal diameter) < the mean for 24 weeks gestation - gestational age is accurate to within 10 days at this phase of pregnancy. Standard obstetric epidemiological data, including those denoting increased risk of premature delivery will be noted.

Women will be randomly allocated by opening a sealed, numbered pre-prepared envelope to one of the two interventions. In the experimental arm they will receive antibiotic treatment on a single occasion between 16-24 weeks (at the time of booking) and again as a second single dose between 28 and 32 weeks (the time of the intervention in the Kenyan studies). Women in the control group will receive oral placebo on both occasions.

For the antibiotic, we propose to use **Azithromycin** **1 gram** given as a single oral dose. Azithromycin is chosen because of its wide spectrum of activity against micro-organisms likely to be associated with preterm labour.23 It also has the advantage of single dose administration, and will likely become less expensive in the near future as the patent expires.

Azithromycin is safe in pregnancy. It is a macrolide antibiotic which is active against a wide range of organisms which are associated with premature labour including, *Neisseria gonorrhoeae*, *Escheridia coli,* *Salmonella* spp., *Chlamydia* and bacterial vaginosis. In addition it is active against gram-negative organisms that have been associated with adverse pregnancy outcome including B haemolytic- streptococci and *Bacteroides spp*.23 Azithromycin is similar to erythromycin but has greater activity than erythromycin against gram-negative bacteria and improved pharmacokinetics with the added advantage that it can be given as a single dose. Mild gastro-intestinal side effects have been noted but otherwise Azithromycin is very well tolerated.23 The gastro-intestinal side effects were noted in one study where 2g doses were given and vomiting was reported in up to 8% of patients. We will give a 1g dose under direct supervision and ask women to report any side effects noted.

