### Sample size

With an estimated incidence of 20% of premature labour, in order to detect a reduction from 20% to 15% with 90% power and a 1 tailed test of significance at the 5% level, 987 women are needed per arm. With a 15% dropout rate this would mean a total of 2 270 women recruited into this trial. If the incidence of premature labour should prove to be 15% this sample size will detect a reduction of 4.6% from 15% to 10.4% (with 90% power).

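### The primary comparison is an unadjusted 2x2 test although prognostic booking data are already collected; pre-specified adjustment would be a small, optional gain in precision

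*Protocol*

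**What the plan says.** The protocol's Data management and analysis section fixes the test for preterm birth: "Analysis of the primary outcome will be using a two by two table and Pearson X2 statistic". Its only mention of regression follows the secondary outcomes: "Association with anaemia status, iron status and malaria parisitaemia will be examined using logistic regression". That sentence names neither the outcome being modelled nor whether allocated arm is in the model.

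Methods says of data at entry: "Standard obstetric epidemiological data, including those denoting increased risk of premature delivery will be noted". It also offers haemoglobin, malaria and syphilis tests and an ultrasound scan at booking, and names four clinics. The Introduction identifies one relevant risk factor: "Women who have had one premature delivery are at increased risk of this complication recurring in future pregnancies". It also reports preterm delivery in 20.7% of non-anaemic, 24.7% of anaemic and 29.7% of severely anaemic women in an earlier study in the same area.

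The Sample size section plans "in order to detect a reduction from 20% to 15% with 90% power" and "a 1 tailed test of significance at the 5% level", and concludes that "987 women are needed per arm". It then adds: "With a 15% dropout rate this would mean a total of 2 270 women recruited into this trial".

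**The concern.** In a randomised trial, adjusting the treatment comparison for baseline variables that predict the outcome, named in advance, generally gives at least the precision of the crude comparison. Here the variables are collected anyway, so the gain needs no extra patients or visits. The design also sits close to its own target: 2,270 women less 15% leaves about 965 per arm, slightly under the 987 required.

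There is a second, smaller reason to name the covariates. Anaemia and malaria are measured again after allocation. The Objectives treat maternal anaemia as an outcome, and Methods raises a possible protective effect of azithromycin against malaria. If regression is later brought to bear on the treatment comparison, follow-up values could already carry a treatment effect. A list restricted to booking values removes that risk and prevents covariates from being chosen after the data are seen.

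**Working it through.** **Inputs from the protocol.** Rates 20% and 15%; one-tailed 5%; 90% power; 987 per arm; 2,270 in total; 15% dropout (Sample size). Preterm rates by anaemia 20.7/24.7/29.7%, and 72% of the population anaemic (Introduction).

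**Assumptions not in the protocol.** Share of women severely anaemic, 0-20%. The 24.7% rate is applied to anaemic women who are not severely anaemic. Prevalence of previous preterm birth 5-20%, with relative risk 1.5-3.

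**1. The plan's own figure.** Without continuity correction, with p̄ = 0.175 and d = 0.05:

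n = [1.645·√(2·0.175·0.825) + 1.282·√(0.20·0.80 + 0.15·0.85)]² / 0.05² = [1.645·0.5374 + 1.282·0.5362]² / 0.0025 = 987.2

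This is 988 rounded up, against 987 stated. The design is powered for an unadjusted one-tailed comparison and does not rely on adjustment.

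**2. Expected number analysed.** 2,270 × 0.85 / 2 = 964.75 per arm. Power = Φ[(0.05·√n − 1.645·0.5374) / 0.5362], which gives 90.0% at 987 and 89.4% at 964.75.

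**3. Variance explained.** R² = (between-stratum variance of risk) / [p(1 − p)], where p is the overall risk.

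- Anaemia, no severe stratum: p = 0.28·0.207 + 0.72·0.247 = 0.2358. Between-stratum variance = 0.28·0.0288² + 0.72·0.0112² = 0.000323. R² = 0.000323/0.1802 = 0.0018.
- Anaemia, 20% severe (weights 0.28/0.52/0.20): p = 0.2458, variance 0.000947, R² = 0.000947/0.1854 = 0.0051.
- Previous preterm birth, 20% prevalence, relative risk 3, overall risk 0.175: risks are 0.125 and 0.375. Variance = 0.8·0.05² + 0.2·0.20² = 0.010. R² = 0.010/0.1444 = 0.069.
- Previous preterm birth, 5% prevalence, relative risk 1.5: R² = 0.0024.

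**4. Effect on power.** Adjustment is taken to act like raising n to n/(1 − R²). One-tailed 5%, 20% vs 15%:

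| R² | Power from 987 per arm | Power from 964.75 per arm |
|---|---|---|
| 0 | 90.0% | 89.4% |
| 0.0051 (anaemia, upper end) | 90.1% | 89.5% |
| 0.02 | 90.5% | 89.9% |
| 0.05 | 91.3% | 90.7% |
| 0.07 | 91.8% | 91.2% |

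At 964.75 per arm, R² of 0.02 is worth 964.75/0.98 − 964.75 = 19.7 women per arm (about 39 in all). R² of 0.05 is worth 50.8 per arm (about 102 in all).

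**Limits.** The 1/(1 − R²) scaling is an approximation suited to a standardised risk difference. R² is computed from pooled marginal risks. The joint R² of several covariates cannot be obtained from the protocol.

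**The case against.** The case for leaving the plan alone is substantial, and most of it stands.

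- **The crude test is not wrong.** It is valid for an individually randomised comparison, its type I error already allows for chance imbalance, and it matches the sample-size basis.
- **A reader might infer that strong predictors are being wasted.** The protocol does not support that. The Introduction itself describes the link between anaemia and preterm delivery as weak at best. It says only that a previous preterm birth raises risk, with no strength or prevalence. Most of the possible gain therefore rests on assumed inputs.
- **A reader might press the point by citing about 82% power.** That figure (82.4% at 965 per arm) comes from replacing the stated one-tailed test with a two-sided one. On the stated basis power is about 89%. Whether a one-tailed basis is appropriate is a separate question that adjustment cannot settle: restoring 90% two-sided power at 987 per arm would need R² of about 0.19.
- **The covariates are imperfect.** The Introduction says that gestation is not reckoned in weeks locally and that losses are distinguished only around seven months, so recalled preterm birth will be misclassified. It is undefined in first pregnancies and is not named as a recorded item. Booking tests are offered, so some values may be missing.
- **An adjusted analysis may already be intended.** The regression sentence is too brief to show that arm is excluded, and a supporting adjusted analysis could sit in an analysis plan that is not shown.

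These points reduce the size and urgency of the suggestion. They do not show that it would do harm if the 2x2 test is kept in support. The choice of primary test, unlike a covariate list, is something this protocol does fix.

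**Conclusion.** The point holds as an optional efficiency improvement of low priority. The primary analysis as written is sound and consistent with its sample size, and it leaves a little precision unused. On the protocol's own figures the gain is about 0.1 power point. With previous preterm birth at 5-20% prevalence and relative risk 1.5-3, both assumed, it is about 0-2 points, and recall error or missing values would pull it down. At the expected 965 per arm, R² of about 0.023 would bring one-tailed power back to the 90% target. That is within the assumed range but well above what anaemia alone provides.

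The documents do not support reading this as an invalid analysis, as a serious loss of power, or as a remedy for the one-tailed design.

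**What to change.** If the sponsor wishes to take the gain, amend Data management and analysis before unblinding as follows:

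- Make the primary treatment comparison a logistic regression of preterm birth on allocated arm, adjusted for a short named list of booking values only: clinic; obstetric history of preterm birth or late loss, with a separate category for first pregnancy; booking haemoglobin; booking malaria result; and gestation at the booking scan.
- State a simple rule for missing covariates, such as a missing-indicator category for untested women, so that nobody is dropped for lack of a booking test.
- Report the standardised risk difference with its confidence interval, which keeps the result on the scale used for the sample size.
- Keep the 2x2 table and Pearson test as a supporting analysis.

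The cost is a few sentences of text, slightly more analysis work and the missing-covariate rule. No new data, visits or participants are needed if obstetric history is recorded on the entry form, which should be checked. The one-tailed versus two-sided question should be dealt with separately.

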### **Presentation and dissemination of results**

Results of this trial will be presented at both local and international meetings. Results will first be presented and discussed in local meetings such as the College of Medicine’s annual Research Dissemination Meeting, weekly departmental meetings in the Dept of Obstetrics & Gynaecology, COM and QECH, and the Wellcome Trust annual meeting. Results will also be disseminated to the community in which work has taken place and to staff from the various sites involved in the project.

Publication of results will be in the Malawi Medical Journal and in regional and international journals.

# Ethical considerations

Consent forms are enclosed with this application. The trial will be introduced to the community via a series of community meetings. This has been successfully organised in the past via the relevant local community leaders. The trial will also be explained at antenatal clinics both as part of information given to the group of women attending as a whole as well as to individual women who are attended to.

As has been our practice in the past, the team of midwives and laboratory technicians from the project will work together with existing staff in the institutions in which we work such that all staff together provide optimum ante- and post-natal care. Services such as blood testing for haemoglobin, malaria parasitaemia, screening for syphilis and ultrasonography will be available to all women attending the clinics i.e. not only to women who agree to enter the proposed trial.

**Possible constraints**

Problems with recruitment:

This is a large trial and we may have problems recruiting sufficient numbers of women into the trial. We will establish two teams of midwives who will work at up to four selected sites together with existing staff. As a result of previous work in the district we have established good links both with the communities and staff of the health facilities in this area. Should recruitment be insufficient from the sites chosen we will expand to recruit in two further sites such as Bangwe Health Centre and/or PIM clinic.

Loss to follow up:

We are aware from previous work that it may not be possible to follow up all patients throughout their pregnancies and into the postnatal period. This may be because people decide to discontinue with the trial e.g. because they are not happy to provide a (further) blood sample, because they move or because they lose the index pregnancy e.g. a late miscarriage. All efforts will be made to visit women who are no longer attending clinic at home. Women who wish to discontinue with the trial will continue to receive antenatal and postnatal care provided by the team. From previous experience we estimate a dropout rate of 15% and have adjusted the sample size accordingly.

##### Training

Training will be organised for staff working at the various facilities, which will focus on premature delivery, infections and malaria. A series of ten 3-day workshops is envisaged

The Wellcome Trust will be approached to fund staff to attend the 3-month course in Reproductive Health for Developing Countries. This is run jointly by the Royal College of Obstetricians (RCOG) and the Liverpool School of Tropical Medicine. This course leads to a Diploma in Reproductive Health from the RCOG.

It is anticipated that at least 2 people from the Department of Obstetrics and Gynaecology will be selected by the Department of Obstetrics and Gynaecology to obtain this Diploma. In addition funding will actively be sought from the Liverpool School of Tropical Medicine, The British Council and the Dutch Government to enable more people to attend this course.

**NB copies of papers in bold have been submitted previously to the COMRC and can be provided again if required.**
